## Abstract

**Background:**

CAREX Canada has identified solar ultraviolet radiation (UV) as the second most prominent carcinogenic exposure in Canada, and over 75 % of Canadian outdoor workers fall within the highest exposure category. Heat stress also presents an important public health issue, particularly for outdoor workers. The most serious form of heat stress is heat stroke, which can cause irreversible damage to the heart, lungs, kidneys, and liver. Although the need for sun and heat protection has been identified, there is no Canada-wide heat and sun safety program for outdoor workers. Further, no prevention programs have addressed both skin cancer prevention and heat stress in an integrated approach. The aim of this partnered study is to evaluate whether a multi-implementation, multi-evaluation approach can help develop sustainable workplace-specific programs, policies, and procedures to increase the use of UV safety and heat protection.

**Methods/design:**

This 2-year study is a theory-driven, multi-site, non-randomized study design with a cross-case analysis of 13 workplaces across four provinces in Canada. The first phase of the study includes the development of workplace-specific programs with the support of the intensive engagement of knowledge brokers. There will be a three-points-in-time evaluation with process and impact components involving the occupational health and safety (OHS) director, management, and workers with the goal of measuring changes in workplace policies, procedures, and practices. It will use mixed methods involving semi-structured key informant interviews, focus groups, surveys, site observations, and UV dosimetry assessment. Using the findings from phase I, in phase 2, a web-based, interactive, intervention planning tool for workplaces will be developed, as will the intensive engagement of intermediaries such as industry decision-makers to link to policymakers about the importance of heat and sun safety for outdoor workers.

**Discussion:**

Solar UV and heat are both health and safety hazards. Using an occupational health and safety risk assessment and control framework, Sun Safety at Work Canada will support workplaces to assess their exposure risks, implement control strategies that build on their existing programs, and embed the controls into their existing occupational health and safety system.

## Background

### Skin cancer and heat stress

The global incidence of skin cancers (both cutaneous malignant melanoma (CMM) and nonmelanoma skin cancers (NMSCs)) has continued to rise over the last decade with up to 3 million cases of NMSCs and 132,000 cases of CMMs occurring each year [1]. This means that one in every three cancers diagnosed is a skin cancer [1]. For Canada, the incidence rate of skin cancers continues to increase. NMSCs are the most commonly diagnosed cancer, with an estimated 76,100 cases and 320 deaths in 2014. In addition, it is estimated that there will be 6,500 new cases of and 1,060 deaths from melanoma in Canada in 2014 [2]. From an economic perspective, the direct and indirect costs of skin cancer for Canada have been estimated to be over $531 million in 2004, with this number projected to rise to over US$921 million by 2031 [3]. Heat stress also presents an important public health issue, particularly for outdoor workers [4]. The most serious form of heat stress is heat stroke, which can cause irreversible damage to the heart, lungs, kidneys, and liver; it has been found to be associated with increased risk of cardiovascular disease, ischemic heart disease, and chronic liver and renal failure.

The most important risk factor for developing skin cancer is exposure to ultraviolet (UV) radiation [5, 6], with occupational solar exposure contributing greatly to overall lifetime UV dose and resulting in an excess risk of skin cancer [7]. The European Community has also identified occupational exposure to UV radiation as one of the most important physical risks in the work environment [8]. Therefore, when the impacts of heat-related conditions are considered in combination with skin cancer, the importance of effective occupational sun safety becomes apparent.

Typical outdoor worker exposures are between 30 and 50 % of the ambient UV levels [9], but these can rise to over 100 % of the ambient UV level in occupations that work in highly reflective environments [10]. No studies on personal UV exposure of outdoor workers have been undertaken in Canada [11]. Outdoor workers tend to spend a significant proportion of their workday in the sun, e.g., in Canada, 67 % of outdoor workers spend two or more working hours in the sun daily [12]. However, workers in the construction, agriculture, forestry, and fishing sectors report even higher daily exposure [13]. In Canada, there are between 1.5 [11] and 5.4 million outdoor workers [12], with CAREX Canada identifying solar UV as the second most prominent carcinogenic exposure in Canada following shift work. However, unlike shift work, solar UV is a known human carcinogen with over 75 % of Canadian outdoor workers falling within the highest exposure category [14].

### Occupational sun safety measures

The World Health Organization recommends that sun protection be provided once the UV index exceeds 3 [15]. For Canada, this means UV protection should be used between April and August in many locations (e.g., in Edmonton), with this extending from March through October in some locations (e.g., in Toronto) [16]. For outdoor workers, general protection measures include the following: engineering controls (for example, the provision of shade, window tinting); administrative controls (educational programs, recognition of individual susceptibilities, sun avoidance strategies, and scheduling of work hours outside of peak UV times); and personal protective equipment (PPE) (wide-brimmed hats, long-sleeved shirts and long pants, use of sunscreen, and eye protection) [17]. These measures should be part of a broader risk management approach that also includes implementing workplace policies and a risk management process [18].

Despite the wide-spread availability of educational materials and sun safety resources (for example, the Canadian Dermatology Association’s Sun Safety for Outdoor Workers Manual or *Be Sunsible*www.besunsible.ca and other resources [19–21]) and the easy availability of a wide range of protection measures, numerous studies have shown that implementing effective sun protection programs for outdoor workers continues to be highly challenging. Few workers are considered to be adequately protected (in some cases 10 % or less) [10, 22–28] with the face and lower arms being the least protected sites [24, 29] and the use of sun screen and wide brimmed hats particularly low [23, 25–27, 30–32]. As such, improving sun protection among outdoors workers is a strategic objective under the Canadian Strategy for Cancer Control [33] and is a key recommendation from the Second National Sun Survey [34].

Control measures for heat stress are well defined and include acclimatization, engineering controls, administrative and work practice controls, and protective clothing [35]. Many of these measures are routinely implemented; however, outdoor workers often have low levels of knowledge regarding appropriate work practices, such as the amount of time required to appropriately acclimatize to hot conditions and the amount of water they should consume [36, 37]. There is also the need to improve workers’ understanding on the benefits of long clothing, including that it does not increase body temperature while providing UV protection [38].

### Sun safety interventions/programs

For many years, there have been community-wide sun safety promotion programs that have focused on skin cancer prevention. A recently completed dynamic simulation modeling exercise to assess the range of sun safety interventions available in four European countries concluded that future interventions should focus on protecting outdoor workers [39]. In the USA and Canada, comprehensive reviews on the effectiveness of sun safety/skin cancer prevention programs have been undertaken [40, 41]. In the USA, the Community Preventive Services Task Force currently recommends multi-component community-wide interventions for skin cancer prevention along with education and policy approaches in outdoor recreation settings [42]. This task force recently updated their advice and, based on the strength of evidence, they now recommend educational interventions that promote sun protective behaviors in outdoor occupational settings to prevent skin cancer. However, evidence gaps still exist regarding the effectiveness of interventions with worksite policy components, such as those that target non-White outdoor workers, and interventions that evaluate health outcomes [43]. A review conducted on behalf of the Canadian Partnership Against Cancer (CPAC) found that there are a range of strategies that are effective for skin cancer prevention, but that success criteria are not currently entirely understood [40]. The National Cancer Institute in the USA maintains the Research Tested Intervention Programs (RTIPs) database that contains details of programs and relevant materials. For sun safety, 17 programs are listed, however, of these, only two relate to outdoor worker interventions (http://rtips.cancer.gov/rtips/index.do).

Five systematic reviews have been conducted in recent years on sun safety interventions for outdoor workers [41, 44–47]. These have concluded that up until recently, there was insufficient evidence to determine the effectiveness of interventions in this setting due to the limited evidence base. However, there is now growing evidence for the effectiveness of sun safety interventions for outdoor workers, while considerable room for improvement remains in occupational sun protection indicating that more research is needed on this topic. In particular, for greatest possible impact, the evidence indicates that a comprehensive workplace strategy that includes multiple interventions aimed at both workers and employers is needed [44]. In addition, there is increasing evidence for the influence of workplace culture on the effectiveness of occupational health and safety interventions [48], and particularly for outdoor sun protection interventions [49]. Six randomized control trials involving outdoor worker sun safety interventions have been identified [22, 50–54]. Two of these studies [52, 53] are included in the RTIPs database. The four most comprehensive intervention projects are SUNWISE (with Southern Californian US Postal Service letter carriers conducted between 2001 and 2004) [53, 55, 56], Go Sun Smart (with employees working at ski areas in North America between 2004 and 2007) [52, 57–61], Pool Cool (with children and lifeguards at swimming pools across the US between 1999 and 2005) [50, 62–66], and the recent QUT Outdoor Workers Project (with small-to-medium rural workplaces in Queensland, Australia) [67, 68].

In summary, although the need for sun and heat protection has been identified, there is a scarcity of projects that have systematically focused on outdoor workers, have addressed both skin cancer prevention and heat stress in an integrated approach, or have specifically investigated occupational sun protection through the lens of integrated knowledge transfer bringing together the expertise of researchers, practitioners, and policymakers.

This paper describes the study protocol for a project funded by the CPAC. CPAC is an independent organization funded by the Canadian federal government that has the mandate to implement the Canadian strategy for cancer control. It funds research projects that are federal and collaborative (among other initiatives). This study was funded under its research program called Coalitions Linking Action and Science for Prevention (CLASP), which is now in its second phase of funding. This project was one of eight that was funded to address issues such as obesity, tobacco use, screening for cancer and chronic disease, and the unique health needs of First Nation communities.

This paper describes the rational and methodology for a workplace-based implementation study for integrated sun and heat safety programs with multiple workplaces. Using an occupational health and safety risk assessment and control framework, the project, called Sun Safety at Work Canada, supports workplaces to assess their exposure risks, implement control strategies that build on their existing programs, and embed the controls into their existing Occupational Health and Safety system. The study also includes a roll-out to raise awareness across workplaces of the danger to outdoor workers of UV exposure through an interactive website and intensive engagement with workplace and policy decision-makers.

## Methods/design

### Research study aims

The aim of the study is to create a nationally applicable sun safety program. The short-term outcomes expected from the project relate to improved employee and employer awareness of the importance of sun safety. This is within the context of improved employer support for sun and heat safety that is demonstrated through the development and implementation of sun safety policies and programs and the commitment of resources to support these policies/programs. The medium-term desired outcomes relate to providing conditions that will enable sun safety programs to be implemented in a sustainable manner. This includes influencing policy and practice to support and enforce workplace sun safety. The long-term desired outcome is the decrease of skin cancer risk and heat-related illness risk for outdoor workers.

#### Two-phased intervention design

The project takes an integrated knowledge translation (IKT) approach that brings together researchers, policy advocates, and practitioners throughout the research process. The partners are Ryerson University’s School of Occupational and Public Health, the Occupational Cancer Research Centre, Sun Safe Nova Scotia, the Occupational Health Nurses Association Nova Scotia, CAREX Canada, Canadian Cancer Society Nova Scotia, Centre for Research Expertise in Occupational Disease, and Alberta Health Services. The study partners have been involved and engaged in the initial conception of the study, the recruitment of workplaces and Sun Safety Advisor knowledge brokers, the creation of the sun safety program suite of resources for workplaces, determining the data that will be collected at three points in time during the study, and the dissemination phases of the study. The partners are based in the four Canadian provinces (Ontario, Nova Scotia, New Brunswick, and British Columbia) in which the interventions will take place and local partners will take the lead in supervising the local interventions.

The research team is interdisciplinary in nature, with researchers from epidemiology, occupational health and safety, occupational medicine, law, sociology, knowledge translation, and adult education. The study uses a mixed methods approach, with the qualitative data analysis being used to help inform and gain a better understanding of the quantitative findings [69]. The project has two complementary phases of activities, in which phase 2 builds on the outcomes of phase 1. Phase 1 is characterized by the intensive engagements with 13 workplaces across Canada and a three-phased evaluation: before the implementation, after the first summer, and 18 months after the project starts (including a second summer). Phase 2 includes an extensive outreach to industry and not-for-profit decision-makers and organizations who are interested in sun protection and policy-level discussions with industry decision-makers, and the creation of a website with tailored resources for workplaces. The process and impact evaluations will be driven by conceptual frameworks to ensure that the phases are theoretically linked and to help us to understand the knowledge translation needs and requirements in rolling out a sun and heat protection programs and policies in workplaces across Canada.

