#### Phase 1: workplace-based sun-safety intervention

The aim of phase 1 is to expand upon the success of existing sun-protection programs by leveraging their findings into the development of a nationally-applicable Canadian-based workplace sun safety program. In this first phase of the study, we will recruit 13 workplaces across four Canadian provinces (i.e., British Columbia, Ontario, Nova Scotia, and New Brunswick) and conduct intensive implementations with the help of Sun Safety Advisors in the role of knowledge brokers. We will work with these workplaces over a period of approximately 18 months.

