#### Phase 1: data collection and analysis

The evaluation will employ a multiple case study approach [81], with the participating workplaces as the units of analysis. The evaluation of the cases will be guided by the conceptual framework for knowledge transfer, dissemination, and utilization for sun safety in outdoor workplaces (Fig. 1) to capture changes in programs, policies, and procedures. Workplace evaluations will occur at three points in time. The baseline assessment will focus on understanding the unique characteristics of each workplace, their occupational health and safety management system, and their current sun safety policy and practices. The second evaluation will be conducted after the first summer (mid-point of the study). The third workplace evaluation will be conducted 18 months after the study’s start date. Finally, a cross-case evaluation matrix will be used to determine generalizable patterns and themes.

Data collection will use mixed methods involving multiple sources of information including semi-structured key informant interviews and focus groups with workers, management, and the occupational health and safety specialist to determine the current occupational health and safety policies and procedure, readiness to change, organizational culture, and barriers/facilitators to sun safety programming (for example, see Fig. 11 information and consent form). The focus groups with employees will explore barriers and facilitators from the perspective of the different workplace parties—workers, supervisors, managers, and occupational health and safety specialists—and a survey will address individual knowledge, attitudes, and behaviors toward sun safety in the workplace. Site observations will record the use of sun safety practices, and a UV dosimetry assessment will measure UV exposure of the employees in the second summer of engagement.

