### Ethics approval

The Community Research Ethics Board (APP7/18/14) has approved this study protocol, and the Research Ethics Board at Ryerson University has deemed that “Based on the information provided the project falls within Article 2.5 of the federal guidelines governing research ethics and so does not require Research Ethics Board review” (REB 2014-263). Participation agreements were signed between the participating project partner agencies. Letters of information will be given out, and written consent will be received by all those engaged in the UV dosimetry study, the interviews, focus groups, and surveys. The letter of information highlights the objective of the study, the composition of the research team, who is eligible to participate, the benefits of being involved in the study, that participation is voluntary, and that all the data collected will remain confidential and accessible only to the research team. It also states that the team expects to finish this study in 2 years’ time (fall of 2016), that we will summarize the study findings and share them with the participating workplaces, and that the results will be put on the project website and the website of the Occupational Cancer Research Centre: http://www.occupationalcancer.ca. We also make the commitment to share our results on posters, at presentations, in newsletters, and in research publications.

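### The third evaluation is set at 18 months from study start, which on the article's own calendar falls before the end of the second summer it is said to include

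*Protocol article*

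**What the plan says.** Four statements in the protocol article bear on when the third evaluation happens.

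- Two-phased intervention design: the evaluations take place "before the implementation, after the first summer, and 18 months after the project starts (including a second summer").
- Phase 1: data collection and analysis: "The third workplace evaluation will be conducted 18 months after the study’s start date". The wave before it is placed relative to the whole study: "The second evaluation will be conducted after the first summer (mid-point of the study").
- Abstract, Methods/design: "This 2-year study is a theory-driven, multi-site, non-randomized study design". Ethics approval reports that the letter of information says the team "expects to finish this study in 2 years’ time (fall of 2016").
- Phase 1: workplace-based sun-safety intervention gives a second 18-month figure, for contact with the workplaces: "We will work with these workplaces over a period of approximately 18 months".

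The data collection section also schedules UV dosimetry for the second summer of engagement. No section prints a start date.

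**The concern.** The third evaluation is described in two ways that do not appear to coincide: as a point 18 months after the start, and as a point that takes in a second summer. If the first summer ends halfway through a 2-year study, month 18 lies between the two summers.

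This is one of only three waves in an uncontrolled before-after comparison, so its timing decides what the last comparison can show. The implementation section has the Advisors leading the education in the first summer. The second summer is therefore where one would look for practices that persist. A wave held before or early in that summer cannot record what workers did during it, and it would precede the dosimetry. It would also set a spring measurement against a post-summer one, so change between the second and third waves could not be separated from season. The article already changes the data collector at that step, from the Advisors to an independent researcher, and a shift of season would add a second difference to the same contrast.

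**Working it through.** The check is calendar arithmetic. No sample size or power figure is involved.

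**Step 1, without any calendar date.** The study lasts 24 months. If the first summer ends at the mid-point, it ends near month 24 / 2 = 12. The second summer ends a year later, near month 12 + 12 = 24. Month 18 is halfway between. For month 18 to follow the second summer, the first would have to end by month 18 − 12 = 6, which is not the mid-point of a 24-month study.

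**Step 2, with the stated finish.** Start = fall 2016 minus 24 months. Fall is taken as 1 September to 21 December, which is an assumption wide enough to cover the usual definitions.

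| Assumed finish | Implied start | Month 12 | Month 18 |
|---|---|---|---|
| 1 Sep 2016 | 1 Sep 2014 | 1 Sep 2015 | 1 Mar 2016 |
| 31 Oct 2016 | 31 Oct 2014 | 31 Oct 2015 | 30 Apr 2016 |
| 21 Dec 2016 | 21 Dec 2014 | 21 Dec 2015 | 21 Jun 2016 |

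Month 12 falls after the summer of 2015, which reproduces the article's own placing of the second evaluation. Month 18 falls between 1 March and 21 June 2016, so it does not follow a second summer.

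**Step 3, size of the gap.** Take summer 2016 to end on about 31 August, with a start between 1 September and 30 November 2014. The end of summer is then month 24 (earliest start) to month 21 (latest start). Ending both seasons about three weeks later gives the same range. Gap = 21 − 18 = 3 months to 24 − 18 = 6 months.

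**Step 4, start dates that might rescue the text.**

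| Start of the clock | Month 18 | Month 24 |
|---|---|---|
| 18 Jul 2014 (an ethics reference read as a date) | 18 Jan 2016 | 18 Jul 2016 |
| 1 Jan 2015 | 1 Jul 2016 | 1 Jan 2017 |
| 1 Mar 2015 | 1 Sep 2016 | 1 Mar 2017 |
| 1 May 2015 | 1 Nov 2016 | 1 May 2017 |

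Month 18 clears the summer of 2016 only if the clock starts in about March 2015 or later. If that were the study's start, 24 months would end in spring 2017 and not fall 2016, and the first summer would end at about month 4 to 6 and not at the mid-point.

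**Step 5, the separate workplace clock.** If 1 March 2015 is the start of workplace engagement, 18 months later is 1 September 2016. A study start of 1 September 2014 leaves 6 months of set-up, and 6 + 18 = 24. This agrees with the 2-year length, the mid-point and the fall 2016 finish. It disagrees only with the words that count the 18 months from the project's or study's start.

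**The case against.** The strongest reply is that the start date is inferred. The 2-year phrase under Ethics approval is reported from a letter of information and counts from that letter. The Advisors' training is placed in a first quarter with no year. Mid-point also serves in the article as a name for the middle wave, so it need not mean exactly month 12. The project overview diagram is not available to check. All of this stands as a limit on how precisely the calendar is known. It does not remove the clash, because the text offers no start date that satisfies the stated length, finish and mid-point and also puts month 18 after a second summer.

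The second reply is that the intention is plain. The 18 months was probably meant to be the period of work with workplaces, following the hiring, recruitment and training listed under Trial status. Step 5 shows that this reading is coherent. It still requires both timing statements to be corrected, since each counts from the project or study start.

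A reader might also infer that the sustainability aim would go unanswered, or that no second-summer data would exist. The documents do not support that. Dosimetry is scheduled for the second summer independently of the month-18 label. The article's major outcomes are changes in policy, procedures and practices, and the first two can be assessed in any season. The medium-term aim concerns conditions that allow programs to be sustained, which is not only a matter of behaviour observed in summer.

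Finally, a spring wave would have one merit: it would sit closer in season to the baseline, which precedes the first summer. That does not help the comparison with the second wave or capture the second summer.

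**Conclusion.** The timing rule is wrong as written. Given a 2-year study, a first summer ending at its mid-point and a fall 2016 finish, month 18 falls in about March to June 2016, some 3 to 6 months before the second summer ends at month 21 to 24. The conclusion rests on an inferred start in about fall 2014 and on ordinary season boundaries. The ordering of month 18 and the end of the second summer needs only the 2-year length and the mid-point statement.

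Followed literally, the rule would weaken the final wave for practices and worker behaviour, place it before the dosimetry and mix season with time in the last comparison. Policy and procedure outcomes would be less affected. If the team in fact counts from workplace engagement, the harm does not arise and only the wording needs repair.

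**What to change.** In Two-phased intervention design and in Phase 1: data collection and analysis, replace the 18 months from project or study start with: after the second summer (fall 2016), in the same season as the second evaluation. Alternatively, define time zero as the start of workplace engagement, and use that definition in both sections and in Phase 1: workplace-based sun-safety intervention. With the second option, engagement should be dated, because Step 4 shows that a start before about March 2015 still puts month 18 inside the summer.

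The cost is a change of wording and, if the literal date was intended, moving one planned wave. The end of summer at month 21 to 24 of 24 leaves about 0 to 3 months for the final wave and its analysis before the stated finish. The comparison of baseline with the final wave would also run from before a summer to after one, as the comparison of baseline with the second wave already does. The Phase 2 section needs no change on this account.
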